### II) Economic evaluation

The economic evaluation will be performed from the societal perspective, which implies that all relevant costs and effects will be taken into account. The economic evaluation compares costs and effects of the ketogenic diet in comparison with usual care. A Cost-Effectiveness Analysis (CEA) and a Cost-Utility Analysis (CUA) will be performed. Outcomes of interest for the CEA and the CUA will be the reduction of seizures and improvement in the Quality Adjusted Life Years (QALYs) respectively. The QALY is a measure of disease burden, including both the quality (utilities) and the quantity of life lived. Total societal costs will be calculated based on the Dutch guidelines for cost calculations in health care. We distinguish four cost categories: intervention costs, health care sector costs, costs for the patient and family, and productivity costs. For this study, three instruments are used to measure the costs and utilities.

#### Prospective cost diary

The diary is used to identify all relevant cost aspects with respect to health care sector costs and patient and family costs [41]. Each diary covers a period of four weeks and will be filled out during the 4 week baseline period and during the 4 month study period. The intervention group will also fill out the diary during the 12 months of follow-up. Total costs will be estimated using a bottom-up approach, where information on each element of service used will be multiplied by an appropriate standardized unit cost and be summed to provide an overall total cost. For the cost valuation, standardized cost prices from the Dutch manual for cost analysis in health care research will be used [42].

#### Productivity losses

A retrospective questionnaire and the patient modules of the PROductivity and DISease Questionnaire (PRODISQ) [43] will be used to measure production losses of the patient's parents. Productivity costs will be calculated by means of the friction cost method, based on a mean added value of the Dutch working population. This method takes into account production losses confined to the period needed to replace a sick employee.

#### Utilities (EQ-5D)

Both generic quality of life, as well as utilities, will be derived by means of the EuroQol, as mentioned before. Utility values will be calculated for all health states of the EuroQol, using preferences from the UK general population value set which provides an algorithm as a series of decrements from 1, the value of full health. Values of the UK population for the scoring function of the health states described by the EQ-5D were measured with the Time Trade Off (TTO) technique (see Torrance, 1976) on a random sample of approximately 3000 members of the adult population of the UK [44]. The utility values derived from the Dolan algorithm will be used to compute Quality Adjusted Life Years (QALYs). However, to overcome the tariff's differences between countries, the Dutch tariff is also used to calculate utilities in the sensitivity analysis. Lamers [45], calculated by means of the TTO method a Dutch scoring function for the health states described by the EQ-5D, based on a Dutch population sample of 300 people.

### Analyses

#### I) Effect evaluation

Our primary (base-case) analyses will be performed according to the intention-to-treat principle, including data from all participants regardless of whether they received the intervention or not. For the analyses we will use SPSS statistical software. Respondents for whom at least 75% of the data per measurement instrument are available will be included in the analysis. Missing data on an item level will be handled using SPSS missing value regression analysis. Completely missing measurements will be handled using multiple imputation. Between-group differences in proportions (dichotomous variables) will be tested using the Chi-square test and between-group differences in means (continuous variables) will be tested using Student's t-test for independent samples. In addition, a multivariate regression analysis will be performed with the covariates of sex, age, severity of disease, duration of disease etc. The accuracy of the findings will be expressed in terms of 95% confidence intervals.

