### Participants

The patient population consists of children and adolescents with drug-resistant epilepsy. Patients are eligible to participate if they meet the following criteria: age between 1 and 18 years old; having uncontrolled seizures; not eligible for epilepsy surgery; no fatty acid oxidation disorders and related diseases; no diabetes and hyperinsulinism; no prolonged QT-time syndrome; no hypercholesterolemia or hypertriglyceridemia; no severe liver, kidney or pancreas diseases; no renal tubular acidosis; no severe behavioral disorder; no malnutrition; no treatment with topiramate or acetazolamide and no positive family history or other risk factors for kidney stones or acidosis.

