##### Neurocognitive assessment

*Peabody Picture Vocabulary test*

The Peabody Picture Vocabulary test (PPVT-III-NL: Dutch version) is an individually administered measure of receptive vocabulary [27]. The test can be administered beginning at the age of 2 1/2 years. The child listens to the examiner's stimulus word and must choose the picture that best describes the word from a 4-picture multiple choice array. The score on this test can be interpreted as an achievement test of the child's vocabulary that does not require a verbal response and as a screening measure of verbal ability. There is supportive data for the validity of the PPVT-III as a measure for global cognitive intelligence.

*Beery Developmental Visual-Motor Integration test*

The Beery Developmental test of Visual-Motor Integration (Beery-VMI) is a widely used assessment of psychomotor development. It measures problems with visual perception, motor coordination, and visual motor integration. The 30-item test can be administered from the age of 2 years. The Beery VMI was standardized on a national US sample of 1,737 individuals age 2 to 18 years (2010) and 1,021 adults ages 19-100 (2006), and has proven reliability and validity [28].

*Fepsy computerized test*

The Fepsy is a neurocognitive computerized test battery consisting of different subtests. For this study we use the simple auditory and visual reaction times, in which the stimulus exposure endures until a push-button (space-bar) response is given [29]. Simple reaction tests give information on alertness functions and on the speed at which the information processing system is activated. We also use the binary choice reaction task in which a combination of accuracy and speed of responses are measured. This test measures the speed of central information processing. Finally, we use the finger tapping task in which motor activation and fluency is measured. In general, these tests can be administered from the age of 6.

*Kaufman Assessment Battery*

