The Kaufman Assessment Battery for Children II (K-ABC II) is used to investigate the level of information processing capacities of children beginning at the age of 2 1/2 years [30]. Two subtests will be administered: (1) Number recall, which is a measure of sequential processing and short term memory. The examiner says a series of numbers and the child repeats them. Digit span forward is considered a measure of efficiency of attention or "freedom from distractibility" and (2) conceptual thinking, which is a measure of nonverbal reasoning skills. The child looks at pictures and determines the one that does not belong.

*Actigraphy*

During the administration of the PPVT-III and the K-ABCII test, an actigraphic device (Actiwatch^® ^model AW4: Cambridge Neurotechnology Ltd., United Kingdom) will be used to assess motor activity as a measure of alertness. As some of the children in the design are not testable with the described cognitive tests we decided to use an assessment of motor activity in a standardized situation. A wrist watch will be used that translates activity into movement of the watch hand. Registration takes place in a standardized way during the first 10 minutes of the Peabody Picture Vocabulary test and the first 5 minutes of the K-ABC-II test. When patients are not eligible to perform the neurocognitive assessment, the wrist watch will be used for 15 minutes during the visit at the nurse practitioner's office while watching a DVD with songs and pictures.

*SEV Questionnaire*

The SEV questionnaire (Sociaal Emotionele Vragenlijst: Social Emotional Questionnaire) is a DSM-IV oriented questionnaire which is used to assess four domains of behavioral and social emotional dysfunction. These domains are: Attention Deficit Hyperactivity Disorders, Oppositional Defiant behavior and Conduct Disorders, Anxiety and Depression, and Autism spectrum disorders. The questionnaire consists of 72 items describing problem behavior [31].

*SDQ Questionnaire*

The Strengths and Difficulties Questionnaire (SDQ) is a brief behavioral screening questionnaire that provides balanced coverage of children and young people's behaviors, emotions, and relationships [32]. The SDQ is applicable to children beginning at the age of 4 and asks about 25 attributes that are divided into five relevant dimensions: namely conduct problems, emotional symptoms, hyperactivity, peer relationships, and pro-social behavior.

*POMS Questionnaire*

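### The 75% completeness rule contradicts the intention-to-treat analysis of all participants and, read plainly, treats partial data worse than no data

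*Protocol article*

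**What the plan says.** Four statements in the protocol article, Analyses, I) Effect evaluation, bear on who is analysed:

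- Analysis population: the primary analysis rests on the "intention-to-treat principle, including data from all participants regardless of whether they received the intervention or not".
- Completeness threshold, given shortly afterwards: "Respondents for whom at least 75% of the data per measurement instrument are available will be included in the analysis".
- Gaps in single items of an instrument: these are to be filled by a regression method in SPSS.
- Measurements absent as a whole: "Completely missing measurements will be handled using multiple imputation".

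No sentence says what happens to a child who has some data on an instrument but less than 75%. None says that such an instrument is reset to missing and then imputed.

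The introduction to the outcome measures (also headed I) Effect evaluation) uses the word instruments for the measurement of seizure frequency, the primary outcome, as well as for the secondary outcomes. The seizure calendar is the tool for seizure frequency.

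On applicability, Participants admits children with "age between 1 and 18 years old". The cognitive tests and questionnaires have narrower age ranges; for the Fepsy battery, "In general, these tests can be administered from the age of 6". Under Actigraphy the article expects that "some of the children in the design are not testable with the described cognitive tests" and provides a motor-activity measure for them.

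**The concern.** An intention-to-treat analysis keeps every randomized child in the arm assigned. A completeness threshold selects children on something that happens after randomization. If completeness is related to response, the selected children are no longer comparable between arms, and the chi-square comparison of success rates inherits that selection.

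The rule also orders the evidence the wrong way round. A child with 60% of an instrument has given information about that child's course. A child with 0% has given none. As written, the second can re-enter through multiple imputation and the first cannot.

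A smaller matter is that regression filling of item gaps, if it is the usual single imputation, puts in one value and then treats it as observed. Confidence intervals based on such data are somewhat too narrow.

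In a trial of 50 children, unblinded for patients and researchers, the composition of the primary analysis set should not be open to interpretation.

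**Working it through.** **1. The rules side by side.** The plan gives no figure for this rule, so the check is mainly one of logic.

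| Share of an instrument available | What the article says, read plainly | Consistent with data from all participants? |
|---|---|---|
| 75% to 100% | included; item gaps filled by regression | yes |
| above 0% but under 75% | not included; no imputation rule stated | no |
| 0% (completely missing) | multiple imputation | yes |

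**2. Does another reading remove the conflict?**

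- *75% counted across visits.* Usual-care children attend T0, T2 and T3, with neurocognitive assessment at T0 and T3 only. One missed visit leaves 2/3 = 67% or 1/2 = 50%, so the child is excluded. For a measure taken at all eight diet-arm time points, two missed visits leave 6/8 = 75%, so the child stays. On this reading a child with 0% is excluded as well, so the inversion in step 1 disappears. The conflict with the inclusion of all participants remains.
- *Under-75% instruments reset to missing and then imputed.* Both the conflict and the exclusion disappear, although the partial data are still unused. The article contains no such sentence.

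**3. Illustration of size.** The article gives no success rates, only a 35-point difference and 22 children per group (Sample Size). Assumed rates are 5% on usual care and 40% on the diet. These are compatible with the plan: a two-sided 5% pooled calculation with 80% power returns 22 per group at a control rate of 5% to 6%. The sample size itself is not disputed.

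- Diet arm, everyone kept: 0.40 × 22 = 8.8 responders; 8.8/22 = 40%.
- Two non-responders excluded: 8.8/20 = 44%.
- Four non-responders excluded: 8.8/18 = 49%.
- Six non-responders excluded: 8.8/16 = 55%.

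The bias does not need one-sided loss. Usual care has 0.05 × 22 = 1.1 responders. If four non-responders are excluded from each arm, usual care reads 1.1/18 = 6%, and the difference is (8.8 − 1.1)/18 = 43 points instead of 35.

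If the four excluded diet children respond at the same 40% rate (4 × 0.40 = 1.6 responders), the result is (8.8 − 1.6)/18 = 40% and there is no bias. The size therefore depends wholly on how strongly incompleteness is related to response.

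**4. Precision.** At the same assumed rates, power is 81.7% with 22 per arm and 72.9% with 18 per arm. Exclusion costs power even when it is unrelated to response.

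**5. Tests that do not apply.** Entry starts at age 1. Beery-VMI starts at 2, PPVT and K-ABC II at 2 1/2, SDQ at 4 and Fepsy at 6; TACQOL covers 6 to 16. The sentence on completely missing measurements does not separate a score that is missing from one that could not exist. If ages were uniform over 1 to 18 (an assumption), (6 − 1)/17 = 29% of children would be below the Fepsy age. That is the share the wording leaves undefined, not a number the plan says it will impute.

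**The case against.** **It may be a scoring rule.** The threshold can be taken to mean that an instrument under 75% complete is not scored and then passes to multiple imputation. That would agree with intention-to-treat. It is a sensible intention, but the text ties the 75% to inclusion of respondents in the analysis, and nothing routes the under-75% group to imputation. A short added sentence would be needed to reach this reading.

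**It may not concern the seizure calendar.** Respondents and item-level gaps are questionnaire vocabulary, and a calendar has no items. This stands in part: application to the primary endpoint is possible, through the general use of the word instruments and the lack of an exemption, but it is not explicit.

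**A reader might infer that early diet stoppers leave partial calendars and drop out of the diet arm only.** The documents do not support this. Nothing says that recording ends when the diet ends, drop-out is defined for both arms, and a visit with neurocognitive assessment is planned on drop-out. The Background reports that the diet should be used for at least 3 1/2 months before a decision to discontinue; 3.5/4 = 87.5% of the 4-month period is above the threshold. It also allows earlier stopping for worsening seizures or uncorrectable adverse effects, so informative gaps remain possible, but only if recording stops as well.

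**A reader might infer that tests a child is too young or unable to take will be imputed.** No sentence says so. The actigraphy substitute, and the choice of TAPQOL or TACQOL by age, show that applicability was considered separately. What stands is that the imputation sentence, read literally, does not exclude it.

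**Item-level regression has limited reach.** Where the 75% rule operates it fills at most 25% of an instrument, and it has no evident role on a calendar. This stands; the effect on interval width is secondary and not quantified.

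**The article condenses a fuller plan.** That excuses omissions. It does not excuse two statements in the same paragraph that disagree about who is analysed.

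**Conclusion.** The point holds as a contradiction within the article. The primary analysis cannot both include data from all participants and admit only those with at least 75% of an instrument. The conflict remains whether the 75% is counted within an instrument or across visits. The finding that partial data fare worse than none holds on the plain reading only.

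The consequence for the primary endpoint is conditional: the rule must be applied to the seizure calendar, and incompleteness must be related to poor response. Under those conditions and the assumed 40% success rate, excluding two to six non-responders among 22 diet children raises apparent success by 4 to 15 points, and four raise it by 9. Against a target difference of 35 points that is material. The success rates and the numbers excluded are illustrative and do not come from the documents.

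Imputation of inapplicable test scores is no more than a point to clarify.

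**What to change.** - Delete the 75% inclusion rule and state that every randomized child is in the primary analysis, in the arm assigned.
- Handle partial and completely missing measurements in one multiple-imputation model that uses the partial data, in place of regression imputation of item gaps. Say explicitly that this covers the seizure calendar.
- Add a sensitivity analysis of the primary outcome that counts children without adequate calendar data at T3 as non-responders, with a definition of adequate.
- As a minor clarification, state that scores on tests outside a child's age range, or that a child cannot take, are treated as not applicable and are not imputed.

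The cost is a few sentences in the Analyses section, a slightly larger imputation model, and somewhat wider confidence intervals, which reflect the uncertainty more honestly. The sample size does not change.

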**Methods/Design:**

In a RCT we will compare the ketogenic diet with usual care. Embedded in this RCT will be a trial-based and model-based economic evaluation, looking from a societal perspective at the cost-effectiveness and cost-utility of the ketogenic diet versus usual care. Fifty children and adolescents (aged 1-18) with intractable epilepsy will be screened for eligibility before randomization into the intervention or the usual care group. The primary outcome measure is the proportion of children with a 50% or more reduction in seizure frequency. Secondary outcomes include seizure severity, side effects/complaints, neurocognitive, socio-emotional functioning, and quality of life. Costs and productivity losses will be assessed continuously by a prospective diary and a retrospective questionnaire. Measurements will take place during consults at baseline, at 6 weeks and at 4 months after the baseline period, and 3, 6, 9 and 12 months follow-up after the 4 months consult.

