Currently the scientific and clinical attention paid to the role of the ketogenic diet is negligible. This means that a ketogenic diet is often overlooked and underutilized as a treatment option for children with intractable epilepsy. An important reason for this is that relatively few children and their parents can comply with the stringent diet. Therefore, physicians are often reluctant to initiate the diet. To offer more children the opportunity to benefit from a ketogenic diet, we suggest that the diet should be initiated and monitored under strictly controlled circumstances in order to maximize compliance.

The beneficial effect of a ketogenic diet has been studied in multiple observational studies [12-20], reviews [21-24] and in one randomized controlled trial [25]. Nevertheless, there is a lack of information about the cost-effectiveness of the ketogenic diet, and consequently health authorities have not been convinced of its usefulness.

The aims of our prospective study are to provide more evidence about the effectiveness and to investigate the cost-effectiveness of treatment with a ketogenic diet KD in comparison with usual care in children and adolescents with drug-resistant epilepsy who are not eligible for epilepsy surgery.

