### Sample Size

A 50% reduction in seizure frequency is considered clinically relevant and is defined as success. Assuming a minimum detectable difference in success rate of 35% between the ketogenic diet group and usual care, and assuming that alpha = 5% and power = 80%, we need 22 children for each group. Taking dropouts into account, we need 50 children in total. A drop-out is defined as a child who drops out of the study before the first consultation with the neurologist; this is scheduled 6 weeks after initiating the KD or 6 weeks after randomization to usual care.

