### Limitations and complications

Compliance with a ketogenic diet is difficult due to its restrictive nature. Unfortunately, non-compliance limits the intended effect and increases the costs to society, resulting in a less favorable cost-effectiveness ratio. In order to overcome this problem, the children and adolescents with uncontrolled epilepsy who are on the ketogenic diet will be monitored according to a strict standardized protocol. Therefore it is likely that the efficiency of patient care will improve. However, a formal assessment of the diet's cost-effectiveness has not yet been performed and is the focus of the present proposal.

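### Multiple imputation for every wholly missing outcome, with no exception for leaving because the diet failed, may overstate the diet's responder rate

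*Protocol article*

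**What the plan says.** The Abstract (Methods/Design) fixes the endpoint: "The primary outcome measure is the proportion of children with a 50% or more reduction in seizure frequency". Sample Size repeats it: "A 50% reduction in seizure frequency is considered clinically relevant and is defined as success". Neither place says how a child who leaves the study is scored.

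Analyses, I) Effect evaluation, sets an intention-to-treat base case covering all participants whether or not they received the intervention. It then gives the only rule for an outcome that is missing altogether: "Completely missing measurements will be handled using multiple imputation". The rule does not distinguish reasons for missingness. It names no donor group and no predictors.

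Elsewhere the article describes why children may stop. Background says the diet may be ended early when seizures worsen or adverse effects cannot be corrected, and that tapering comes earlier for intolerable side effects or ineffectiveness. It also says that "relatively few children and their parents can comply with the stringent diet". Limitations and complications adds: "Compliance with a ketogenic diet is difficult due to its restrictive nature".

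Three provisions bear on how much data a leaver contributes. Timeline of the study provides a team visit at drop-out. Primary outcome, Seizure frequency, has seizures entered by date on a calendar. The intention-to-treat rule keeps a child who stops the diet but stays in follow-up.

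**The concern.** If leaving is a consequence of failure, the missing outcome itself carries information. Imputation under missing at random takes no account of the reason for leaving unless that reason, or something closely tied to it, is in the model. In a diet arm where most observed outcomes come from children still on the diet, some failures would be filled in as successes.

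The problem falls mainly on one arm. The Usual care section has controls simply continue their existing drugs for four months, so they have no diet to fail or abandon. An error in the diet arm is therefore unlikely to be offset by a similar one among controls, and it favours the diet.

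The primary comparison is at stake. With 25 children per arm, one child is 4 percentage points, so a few misclassified leavers matter against a 35-point target.

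**Working it through.** **1. The plan's own figure.** Sample Size takes a 35-point gap in success rate as the smallest to be detected. It concludes: "assuming that alpha = 5% and power = 80%, we need 22 children for each group". The two rates are not given, so the control rate is an assumption. With the pooled two-sided formula, no continuity correction, and 5% against 40% (mean 22.5%):

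n = [1.96 × √(2 × 0.225 × 0.775) + 0.8416 × √(0.40 × 0.60 + 0.05 × 0.95)]² / 0.35² = (1.157 + 0.451)² / 0.1225 ≈ 21.1, hence 22.

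A control rate of 6% also gives 22. The total follows: "Taking dropouts into account, we need 50 children in total", that is 1 − 44/50 = 12% allowed for drop-out, and 12% of 25 is 3 children per arm. The sample size is not in dispute. It supplies the scale for what follows.

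**2. Upper bound of the bias.** Let d be the share of the diet arm leaving with a missing outcome and p the responder rate among those who stay. If every leaver is a true failure, the arm's success rate is p(1 − d). If the imputation uses no on-treatment data, leavers receive p on average and the arm's rate becomes p. The overstatement is p × d.

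Assumptions: 25 per arm, control rate 5%, p = 40%, no control losses.

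| Diet leavers | d | Rate, leavers as failures | Difference | Difference if leavers receive p | Overstatement |
|---|---|---|---|---|---|
| 3 | 12% | 35.2% | 30.2 points | 35.0 points | 4.8 points |
| 5 | 20% | 32.0% | 27.0 points | 35.0 points | 8.0 points |
| 7 | 28% | 28.8% | 23.8 points | 35.0 points | 11.2 points |

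The matching two-sided power is 77.7%, 70.3% and 61.8% at the lower rates, against 86.5% at 40%. These power figures treat imputed values as if observed, so they only approximate what an imputation analysis would give. At p = 60% the overstatement is 7.2, 12.0 and 16.8 points.

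**3. When early seizure data help.** A simulation of 25 diet children (2,000 runs) had 27% leave, driven by a poor 6-week response. The true diet success rate was 42.9%.

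| Handling | Estimated rate | Error |
|---|---|---|
| Imputation without early data | 52.9% | +10.0 points |
| Imputation using the 6-week seizure ratio | 43.7% | +0.8 points |
| Leavers as non-responders | 38.5% | −4.4 points |

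With the early data, leavers were imputed as responders 19% of the time, not at the stayers' 53%.

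**4. When they do not help.** In step 3, leaving is driven by the same variable that the imputation uses, which is close to missing at random by construction. A second simulation assumed about 25% leaving, half of them before week 6, and response lost after stopping. The 6-week ratio was again in the model. With leaving unrelated to early response, true success was 33% and imputation gave 43%. With leaving related to poor response, the figures were 37% and 46%. These agree with step 2: 33% / 0.75 = 44% and 37% / 0.75 ≈ 49% are the stayers' rates, and the imputed rates lie just below them.

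**The case against.** The strongest reply is that the article does not specify the imputation model. A reader might infer that diet failures will be scored as responders at the rate of the children who stayed. The text does not support that. It names no donors or predictors, and that result belongs to a model with no on-treatment data. The model may properly be set out in an analysis plan that is not shown, so its absence here is not an error. This stands, and it makes p × d a ceiling, not an estimate.

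The drop-out visit, the dated calendar and intention-to-treat follow-up also reduce missingness and can supply predictors. That stands too, but only in part. Sample Size counts as drop-outs only those who leave before the 6-week consultation, so the children allowed for there have no 6-week visit. A count made while on the diet does not show the outcome after stopping, and leaving for intolerance need not follow a poor early response.

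The compliance quotes need their context. Background reports a recommended trial of at least 3½ months before discontinuing, and the article plans strict monitoring to maximise compliance. Leaving may therefore be uncommon before the 4-month visit. The article gives no rate beyond the implied 12%.

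Scoring leavers as failures also changes the quantity estimated and can undershoot, as in step 3 of the working (38.5% against 42.9%). This is a fair cost. Scoring every usual-care leaver as a failure but only some diet leavers would itself favour the diet, so the rule must be the same in both arms.

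A reader might also infer that the cost per success is necessarily understated. The economic sections define effect as seizure reduction and as decreased frequency and severity, not as 50% responders, so that does not follow.

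**Conclusion.** The concern holds in a limited form. The stated rule covers every wholly missing outcome, makes no exception for leaving because treatment failed, and sits beside the article's own account of why children stop the diet. The sensitivity analyses that the article names are all economic. The rule can therefore bias the responder difference toward the diet.

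The size is bounded by the share leaving with a missing outcome times the stayers' responder rate: 4.8 to 11.2 points for 12-28% leaving at a 40% stayers' rate. Those rates are assumptions. The bias could be close to nil if leaving follows early response and calendar counts enter the imputation. It could stay near the bound if children leave before week 6 or for intolerance. The documents do not show which case will apply.

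**What to change.** For the 50% responder endpoint, state one rule for both arms:

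- Use the observed 4-month seizure count whenever it exists, whether or not the child is still on the assigned treatment.
- Score a child who leaves before the 4-month visit for lack of effect, worsening or intolerance as a non-responder.
- Keep multiple imputation for missingness unrelated to treatment, such as a lost calendar, with baseline and on-treatment calendar counts as predictors.

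Report two sensitivity analyses: all missing outcomes imputed, and all leavers in both arms scored as non-responders. Carry the same handling into any incremental cost-effectiveness ratio that uses the responder effect.

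The cost is about a paragraph of analysis wording and no new data. The reason for leaving must be recorded in the same way in both arms, which the drop-out visit makes feasible. The downside is a somewhat less favourable diet success rate if early leaving is common.
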